### Informed consent

The RAPTOR-C19 site team will ask eligible and willing patients (or their parent/carer, where applicable) to complete an e-consent process (Supplementary Figure S1). Informed consent will be obtained in line with Good Clinical Practice (GCP) guidelines.

It is imperative that all non-essential contact between the participants, researchers, and practice staff is prevented in order to minimise the risk of SARS-CoV-2 transmission. To achieve this, we will use a combination of digital written consent and/or researcher recorded verbal consent in this study, in person, or remotely by telephone or using video link. Written information will be available in the form of posters at RAPTOR-C19 sites, and as electronic participant information accessible online at https://www.condor-platform.org/condor_workstreams/raptor (Supplementary Figure S2).

The participant will be allowed as much time as wished to consider the information, and the opportunity to question the researcher or other independent parties to decide whether they will participate in the study. All answers will be stored electronically and securely.

### Data collection

RAPTOR-C19 have developed a bespoke data collection solution with uMed, a UK based health-technology company. Through a series of secure webpages, the uMed platform will allow the participant, or the researcher on behalf of the participant, to record eligibility and to document consent. The uMed platform will guide the participant, or the participant’s parents/guardians, through the consent questions, or the researcher will read out the questions from the form, recording the participant’s responses electronically. The completed consent form will be exported into a pdf document and emailed to the participant.

Consenting participants will be asked for further study-specific information, which will be entered into the electronic case report form (eCRF). RAPTOR-C19 will provide study sites with a Wi-Fi- and 4G-enabled tablet to collect study data. However, it will be possible to assess eligibility and to gather consent and additional participant information using any internet enabled device.

ORCHID practices currently share pseudonymised data for surveillance and research twice weekly, with practices migrating to a daily extract. ORCHID data is also linked to hospital and death data to allow robust identification of outcomes. Individual patients volunteering to participate in RAPTOR can have relevant health data linked to the study database.

### Baseline assessments

For adults (≥ 16 years old) study visits will follow the same protocol whether current or past COVID-19 is suspected: the analysis will be different. In children (< 16 years), only those with suspected current COVID-19 will be included. In all cases, the baseline visit will involve the POCT(s) under evaluation and the tests for laboratory reference testing (see below). Following consent being provided, the eCRF will then be used to capture study data as detailed in Supplementary Box S1.

### Index tests and reference standards

#### Index tests (POCTs)

Biological samples to test for current SARS-CoV-2 infection will be collected from all participants. The index test will be at least one, but the intention is to assess multiple, candidate POCTs for active infection (all participants) or past infection (adults only). If multiple POCTs are being assessed, these may target a combination of current SARS-CoV-2 infection and past SARS-CoV-2 infection.

Participants will be asked to submit samples as appropriate for each candidate POCT by following the training and instructions provided by the manufacturer. These may include oropharyngeal/nasopharyngeal (OP/NP) swab, saliva, or blood from a finger prick. POCTs requiring finger prick blood samples will only be offered to participants > 10 years old. For POCTs that require assistance to complete, the researcher will assist the participant whilst adhering to safe PPE use. Where a participant completes the tests themselves, they will be observed by the researcher to monitor correct POCT use and ease of use and to identify sample quality issues.

The order in which the tests are conducted will not be randomised but the sequencing of the tests will be documented in the eCRF. Who performs the test, either participant or researcher, will also be recorded.

All POCT consumables will be discarded as clinical waste as soon as the POCT is complete and the results have been captured. No POCT samples will be retained by the RAPTOR-C19 team.

Both the researcher and the participant will be blinded from results of the reference test, as results will not be returned for at least 24 h after the POCT is taken. For paired index tests blinding will not be possible in a clinical environment. For qualitative index tests, we will capture a photograph of the result, for adjudication by independent research staff, blinded to any other clinical information or test results. POCT results will not be shared with the patient and they must not be used to make any clinical decisions.

POCT-specific amendments to the ethical permission and protocol will be completed prior to including each POCT in the assessment. RAPTOR-C19 staff will develop training materials using the manufacturer’s instructions (these will be edited if deemed necessary by the RAPTOR-C19 and the Patient and Public Involvement group). RAPTOR-C19 staff will liaise with the manufacturers where clarification is required on use of the POCT. They will arrange training via teleconference with local study leads and community staff to allow rapid dissemination in compliance with social distancing advice. Online tutorials and/or YouTube videos will be made available. These will be updated as necessary, as new POCTs are introduced into the study. During the study, RAPTOR-C19 staff will be available to support study sites and answer any queries.

#### Reference laboratory tests

The current PHE reference standard for active infection is an OP/NP swab for laboratory real-time RT-PCR triplex assay for the detection of SARS-CoV-2. It incorporates multiplex detection of two SARS-CoV-2 targets (Orf1ab and E genes) and uses a soil borne cereal mosaic virus internal control [35]. It is important to note that reference laboratory tests for current infection will be done as part of clinical care or as part of the national surveillance system. Individuals can have these done whether or not they agree to be part of research.

Only adult participants (≥16 years old) will be asked to submit a blood sample for antibody testing for use as the reference standard for past SARS-CoV-2 infection and within the composite reference standard (see below) for current infection. Adults will have blood samples for this drawn at baseline and follow-up visits by appropriately trained staff.

Participants will receive clear instructions on how to sample, as per PHE standard advice. If participants are unable to self-swab, or express a preference, a staff member with appropriate training will take the sample. The sample material will fall under PHE or other central testing laboratory and not our study remit, and under current rules PHE may retain the swab for up to 5 years. Participants will be able to discuss the results of the PHE reference standards with their GP.

Once taken, the samples will be put in the regulation container packaging, double bagged, and sent to the PHE laboratory or other central testing centre laboratory that is supporting the study using their existing, safe, quality compliant processes. Participants will have the option to agree to this sample being retained for future surveillance or research use.

We acknowledge that the PHE reference standard and the details of the assay may change throughout the study as more accurate reference tests are adopted. POCTs will always be benchmarked against the current best practice. We will report the reference standard tests used in each POCT evaluation when each evaluation is submitted for publication. We will also compare POCTs to any change reference standards to mitigate the imperfect reference tests, and adjust our statistical analysis to reflect these potential changes.

### Subsequent visits

Where feasible, adult (≥ 16) participants will also be invited to attend a second visit, or visited at home by a research nurse, 28 days following the first visit, to allow for a blood test for repeat antibody testing as outlined above.

Adult participants may be contacted by text message to complete an online daily symptom diary prior to the follow-up visit.

The time schedule of enrolment, assessments, and visits for participants is summarised in Table 2.

**Table 2 Tab2:**
[figure not shown]
Schedule of enrolment, interventions, and assessments for RAPTOR-C19

### Study end

Recruitment will be reviewed by the Study Management Committee, using the latest prevalence data from PHE, as prevalence of SARS-CoV-2 is dynamic and affects the sample size required. Each participant has the right to withdraw from the study at any time. Withdrawn participants will not be replaced. Participants are not required to give a reason for withdrawal. The investigators may discontinue a participant from the study at any time if they consider it necessary for any reason including the following:
Ineligibility (either arising during the study or retrospectively having been overlooked at eligibility assessment)Significant protocol deviationWithdrawal of consentIf the participant declines POCTs, or if an adult (≥ 16 years) declines to give a venous blood sample

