### Primary objective

Assess the standard diagnostic accuracy of POCTs for active SARS-CoV-2 infection compared to the Public Health England (PHE) reference laboratory standard or equivalent

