### Data sources

Table 3 outlines which data sources used to address each research question.

**Table 3 Tab3:** Data sources for analysis

Question	Data source					
	eCRF	*POCT index test* for *active* COVID-19	*Laboratory reference test* for *active* COVID-19	*POCT index test* for *past* COVID-19	*Laboratory reference test* for *past* COVID-19	*Composite reference standard*
*Standard* diagnostic accuracy of *active* infection	Yes	Yes—visit 1. Current and past suspects	Yes—visit 1. Current and past suspects	No	No	No
*Enhanced* diagnostic accuracy of *active* infection	Yes	Yes—visit 1. Current and past suspects	Yes—visit 1. Current and past suspects	No	Yes—visit 2. Current and past suspects	Yes
*Standard* diagnostic accuracy of *past* infection	Yes	No	No	Yes—visit 1. Current and past suspects	Yes—visit 1. Current and past suspects	No
*Enhanced* diagnostic accuracy of *past* infection	Yes	Yes—visit 1. Current and past suspects	Yes—visit 1. Current and past suspects	Yes—visit 1. Current and past suspects	Yes—visit 1 and 2. Current and past suspects	Yes

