However, in the pandemic situation, community testing has been expanded in unexpected and unprecedented ways. In order to respond to the needs of the community and maximise recruitment and coverage of different clinical settings, we may also recruit from other community settings where reference RT-PCR swabs are being or can be collected. These might include national testing centres, home testing systems, surveillance and national telephone triage services, pop-up community laboratories in areas of increasing local prevalence, transport infrastructure and the UK borders, and educational or commercial organisations. People tested at these locations will not necessarily be registered at RCGP RSC practices, and the venues may not be able to undertake venepuncture, so it may not be possible to use the same reference standards as at GP practices. Many of these settings undertake service evaluations that align with government priorities, and we would seek to partner with these organisations. We would aim to establish data sharing agreements for a limited set of de-identified participant and test result data to permit the primary evaluation of POCTs used in these settings against the usual RT-PCR reference standard, and depending on the data they are able to collect, modified enhanced standards.

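### Adults who decline venous blood may be discontinued although the primary active-infection analysis uses no blood; as written, the rule could remove valid POCT/RT-PCR pairs and select the adult sample

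*Protocol article*

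**What the plan says.** Study end gives investigators a discretionary power: "The investigators may discontinue a participant from the study at any time if they consider it necessary for any reason including the following". One item in the list that follows joins two refusals, that of the POCT and that of blood: "if an adult (≥ 16 years) declines to give a venous blood sample". The item does not say whether it means the baseline draw, the day-28 draw or both. Earlier in the same section, after the participant's right to withdraw, stands "Withdrawn participants will not be replaced".

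The primary objective is "Assess the standard diagnostic accuracy of POCTs for active SARS-CoV-2 infection compared to the Public Health England (PHE) reference laboratory standard or equivalent". Reference laboratory tests defines that standard: "The current PHE reference standard for active infection is an OP/NP swab for laboratory real-time RT-PCR triplex assay for the detection of SARS-CoV-2". The same section says that adult blood is taken "for use as the reference standard for past SARS-CoV-2 infection and within the composite reference standard (see below) for current infection". Those are secondary objectives.

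Four other places bear on the rule:

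- **Table 3 (Data sources):** the row for standard accuracy of active infection has Yes for the eCRF, the active POCT and the active laboratory reference. It has No for the laboratory reference for past infection and No for the composite.
- **Table 1:** willingness to give blood is not an inclusion criterion, and declining it is not an exclusion criterion.
- **Subsequent visits:** the day-28 visit for repeat antibody testing is offered only where feasible.
- **Strengths and limitations:** at possible further settings, "the venues may not be able to undertake venepuncture". The article still aims for a primary evaluation there against the usual RT-PCR reference.

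**The concern.** Declining the POCT removes the index test, so no accuracy analysis of that test is possible. Declining venous blood removes only a reference used in secondary analyses. The discontinuation rule treats the two alike.

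Two things are at stake for the primary estimate. The first is precision, since each lost pair from a reference-positive adult reduces the denominator of sensitivity. The second is spectrum. Participant selection aims at all-comers, and the Background warns of spectrum bias and says that tests must work in elderly and frail patients. A rule that can make adult inclusion depend on accepting venepuncture works against that aim. Because its use is discretionary, it could also be applied differently from site to site. It touches adults only, while primary results are to be stratified by adults versus children and by age group.

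**Working it through.** **Step 1. Does the primary analysis use the blood sample?** The primary objective, the definition of the reference standard and the standard/active row of Table 3 agree that it does not. Blood enters the other three rows: standard past, enhanced past and enhanced active. In the enhanced active analysis, Table 4 also uses a later RT-PCR and hospital admission or death. An adult without serology therefore still has part of the composite information.

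**Step 2. Reproduce the plan's figures.**

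- Table 5, sensitivity 90%, standard error 2.5%, prevalence 30%: reference-positives = 0.9 × 0.1 / 0.025² = 144; participants = 144 / 0.30 = 480, as stated. All 48 cells of the table reproduce by this formula, rounded up.
- Stopping criteria, 200 participants at 30% prevalence: 200 × 0.30 = 60 reference-positives. The 5% scenario gives the same count: 1200 × 0.05 = 60.

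No stated number is wrong.

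**Step 3. Size of a possible loss.** The article gives no refusal rate. Let *d* be the share of all participants whose pair is lost. Assume that every decliner is dropped and that decliners have the same prevalence as the rest. Then pairs left = N(1 − d), standard error (SE) = √[0.9 × 0.1 / (N(1 − d) × 0.30)], and recruitment needed to restore N = N/(1 − d), rounded up.

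| Start | d | Pairs left | Positives left | SE, points | Recruit to restore N |
|---|---|---|---|---|---|
| 200 | 0 | 200 | 60 | 3.87 | 200 |
| 200 | 5% | 190 | 57 | 3.97 | 211 |
| 200 | 10% | 180 | 54 | 4.08 | 223 |
| 200 | 20% | 160 | 48 | 4.33 | 250 |
| 480 | 0 | 480 | 144 | 2.50 | 480 |
| 480 | 5% | 456 | 136.8 | 2.56 | 506 |
| 480 | 10% | 432 | 129.6 | 2.64 | 534 |
| 480 | 20% | 384 | 115.2 | 2.80 | 600 |

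Example: √(0.09 / 48) = 4.33 points.

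The rule does not apply to children, so *d* is at most the refusal rate among adults. If 80% of participants were adults (an assumption) and 20% of them refused, d = 0.16. From 200 that leaves 168 pairs and 50.4 positives, and the SE is √(0.09 / 50.4) = 4.23 points.

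**Step 4. Selection.** The shift is the sensitivity among acceptors minus [(1 − d) × sensitivity among acceptors + d × sensitivity among decliners]. With 90% and 70% as illustrative values and d = 20%: 0.90 − (0.8 × 0.90 + 0.2 × 0.70) = 0.90 − 0.86 = 4 points too high. With equal sensitivity in both groups the shift is 0. The article gives no information on which case applies.

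**The case against.** The strongest reply is that the rule is permissive and that the article never says results already collected are discarded. A reader might infer that refusers are excluded from the primary analysis, but the text does not support that. Discontinuation is from the study, at discretion, and may come after the pair exists, above all when the refusal is at day 28. What happens to data collected earlier may be settled in the full protocol or the SAP, which are not shown. This stands, and so loss and selection are possible consequences of the rule, not certain ones.

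Four further inferences also go beyond the text:

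- **No replacement.** The sentence speaks of withdrawn participants and precedes the list of investigator discontinuations. It does not plainly cover the latter. The sample sizes are also called indicative and illustrative, so no fixed total is being eroded.
- **Consent.** Table 1 does not require blood, but the consent wording is in supplementary figures that are not shown.
- **Pooling.** The venues without venepuncture are a possible extension, and nothing says that their data join those of general practices in one analysis.
- **Bias.** It needs POCT accuracy to differ by refusal, and the documents give no evidence that it does.

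It can also be said that serology serves all three secondary objectives and that adults follow one visit protocol, so the rule reflects a design trade-off. This part fails. Discontinuing a person who has refused blood yields no extra serology, while keeping that person preserves the primary pair. The missing-data section promises to report missing test results, to examine their association with patient characteristics and to run sensitivity analyses. That helps with absent results, but it does not address a rule that permits removal on this ground.

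**Conclusion.** The point holds as a badly fixed rule. The article permits discontinuation for lack of a sample that its primary analysis does not use, its eligibility table does not require, and its own Discussion is ready to do without elsewhere. The rule could cost valid pairs and could select adults on willingness to have venepuncture. The article does not establish that either will happen.

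The loss of precision is modest. With 5–20% refusal among adults, every decliner dropped and all participants adult (an upper bound), 3–12 of 60 reference-positives are lost and the standard error at 90% sensitivity rises from 3.9 to at most 4.3 points. The refusal rate is an assumption. The size and direction of any selection bias cannot be determined from the article, and it may be zero. The change is worth making because the rule brings the primary analysis no benefit and is easily removed.

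**What to change.** In Study end, remove refusal of venous blood from the reasons for discontinuation. Add a sentence on three points:

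- An adult who declines blood at baseline or at day 28 stays in the study.
- The refusal affects only the past-infection analyses and the serology component of the composite standards.
- Any available POCT/RT-PCR pair stays in the standard active-infection analysis unless consent for its use is withdrawn.

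The cost is a short protocol edit and more participants with missing serology in the enhanced analyses. These can be reported, with their characteristics, under the existing missing-data plan.

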### Safety

All RAPTOR-C19 sites will be required to follow the current PHE infection prevention and control guidance regarding collection and processing of samples at all times including that regarding PPE. Contact will be minimised by using electronic and/or verbal consent, where possible remotely by telephone or video calls.

Safety reporting is not applicable given the low risk of point-of-care tests. Nose and throat swabs cause some transient discomfort to patients, but there are no clinically significant risks associated with the procedure. Fingerstick blood sampling may cause transient discomfort and localised bruising at the sampling site; however, there are no clinically significant risks associated with the procedure. Venous blood sampling causes discomfort and may result in bruising and localised swelling at the sampling site. Provision of saliva samples is unlikely to cause discomfort to any participants. To mitigate these risks, self-sampling will be supported where appropriate, otherwise these procedures will be carried out by personnel who have received training in these procedures or who carry out these procedures as a routine element of their duties.

A serious adverse event is any untoward medical occurrence that does the following:
Results in deathIs life-threateningRequires inpatient hospitalisation or prolongation of existing hospitalisationResults in persistent or significant disability/incapacityConsists of a congenital anomaly or birth defect

Serious adverse event (SAE) occurring to a participant will be reported to the REC that gave a favourable opinion of the study where in the opinion of the Chief Investigator the event was ‘related’ (resulted from administration of any of the research procedures) and ‘unexpected’ in relation to those procedures. Reports of related and unexpected SAEs will be submitted within 15 working days of the Chief Investigator becoming aware of the event, using the Health Research Authority (HRA) report of serious adverse event form (see HRA website).

### Statistics and analysis

The statistical aspects of the study are summarised here with details fully described in a statistical analysis plan (SAP). The SAP will be finalised before any analysis takes place.

### Data sources

Table 3 outlines which data sources used to address each research question.

**Table 3 Tab3:** Data sources for analysis

Question	Data source					
	eCRF	*POCT index test* for *active* COVID-19	*Laboratory reference test* for *active* COVID-19	*POCT index test* for *past* COVID-19	*Laboratory reference test* for *past* COVID-19	*Composite reference standard*
*Standard* diagnostic accuracy of *active* infection	Yes	Yes—visit 1. Current and past suspects	Yes—visit 1. Current and past suspects	No	No	No
*Enhanced* diagnostic accuracy of *active* infection	Yes	Yes—visit 1. Current and past suspects	Yes—visit 1. Current and past suspects	No	Yes—visit 2. Current and past suspects	Yes
*Standard* diagnostic accuracy of *past* infection	Yes	No	No	Yes—visit 1. Current and past suspects	Yes—visit 1. Current and past suspects	No
*Enhanced* diagnostic accuracy of *past* infection	Yes	Yes—visit 1. Current and past suspects	Yes—visit 1. Current and past suspects	Yes—visit 1. Current and past suspects	Yes—visit 1 and 2. Current and past suspects	Yes

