### Composite reference standards

An assumption of standard diagnostic accuracy studies is that the reference standard is infallible. This constrains the performance of the index test to the performance of the reference standard and assumes every time the tests get different results the reference is correct and the index is incorrect. There is evidence of substantial heterogeneity of diagnostic accuracy of SARS-CoV-2 d/rRT-PCR testing, with reported false negative rates of 18–58% [36]. Both clinical context and repeated testing are highly relevant to calculating the likelihood of true negative cases [37], and so we will undertake further analyses using the composite reference standard.

Composite reference standard 1 will be designed to minimise false negatives (FNs), and composite reference standard 2 will be designed minimise false positives (FPs). Both composite reference standards will be constructed considering paired antibody test results, patient reported outcomes, linked EHRs for outcomes related to COVID-19, such as hospitalisation or death, other test results (Table 4).

**Table 4 Tab4:** Potential use of tests to enhance the reference standard. Information in the table refers to hypothetical combinations of results in which the enhanced reference standard result would be considered different from the original reference standard result. A cell-by-cell interpretation of each scenario follows.

	Minimise FN for current infection		Minimise FN for past infection	
Visit (day)	1 (0)	2 (28)	1 (0)	2 (28)
**SARS-CoV-2 RT-PCR**	Negative (FN)	N/A	Negative	N/A
**COVID IgG**	Negative	Positive	Negative (FN)	Positive
Or:	Subsequent positive SARS-Cov-2 RT-PCR result (within 28 days)		-	
Or:	Hospital admission or death (within 28 days) citing SARS-CoV-2 as probable cause		Hospital admission or death (within 28 days) citing SARS-CoV-2 as probable cause	
	**Minimise FP for current infection**		**Minimise FP for past infection**	
**Visit (day)**	1 (day 0)	2 (28)	1 (day 0)	2 (28)
**SARS-CoV-2 RT-PCR**	Positive (FP)	N/A	Negative	N/A
1.1.35. **COVID IgG**	Negative	Negative	Positive (FP)	Negative
And:	No subsequent positive SARS-Cov-2 RT-PCR result (within 28 days)		-	
And:	No hospital admission or death (within 28 days) citing SARS-CoV-2 as probable cause		No hospital admission or death (within 28 days) citing SARS-CoV-2 as probable cause	

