Minimise FN (false negative) for current infection: If the COVID-19 RT-PCR reference test gives a negative result, it can be considered a false negative if the IgG result is positive at 28 days (newly positive or titres have increased), OR if a subsequent SARS-Cov-2 RT-PCR result (within 28 days) was observed, OR if there was a hospital admission or death (within 28 days) citing SARS-CoV-2 as probable cause

Minimise FP (false positive) for current infection: If the COVID-19 RT-PCR reference test gives a positive result, it can be considered a false positive if the IgG result is negative at both baseline and 28 days, AND if no subsequent SARS-Cov-2 RT-PCR result (within 28 days) was observed, AND if there was no hospital admission or death (within 28 days) citing SARS-CoV-2 as probable cause

Minimise FN (false negative) for past infection: If the baseline reference IgG test result is negative, it can be considered a false negative if the 28-day IgG test result is positive, OR if there was a hospital admission or death (within 28 days) citing SARS-CoV-2 as probable cause

Minimise FP (false positive) for past infection: If the baseline reference IgG test result is positive, it can be considered a false positive if all other tests at baseline and at 28 days are negative, AND there has been no hospital admission or death (within 28 days) citing SARS-CoV-2 as probable cause

Paired antibody testing at 0 and 4 weeks will identify changes in antibody levels over time. These serial laboratory samples will allow us to identify antibody changes to discriminate between current and past infection, and to highlight possible FP and FN RT-PCRs, whilst it remains possible that infection could occur after the index test but prior to the day 28 serology sample, this is unlikely to be a frequent event.

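### Table 3 gives the enhanced active-infection analysis only the day-28 antibody result, although its composite rules need both visits, and pooling past suspects lets some recovered people count as current cases

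*Protocol article*

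**What the plan says.** All places are in the protocol article.

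- **Data sources, Table 3.** For enhanced accuracy in active infection, the laboratory antibody entry is "Yes—visit 2. Current and past suspects". For enhanced accuracy in past infection, it is "Yes—visit 1 and 2. Current and past suspects". Every row pools the two groups of suspects.
- **Composite reference standards, opening text.** "Both composite reference standards will be constructed considering paired antibody test results, patient reported outcomes", together with linked records and other test results.
- **Table 4, current infection, minimising false negatives.** PCR negative at day 0, with IgG negative at day 0 and positive at day 28; or a later positive PCR; or a COVID-related admission or death.
- **Text below Table 4, same rule.** For a negative PCR, "it can be considered a false negative if the IgG result is positive at 28 days (newly positive or titres have increased". A COVID-related admission or death also qualifies. The criterion on later PCR testing is worded "if a subsequent SARS-Cov-2 RT-PCR result (within 28 days) was observed", without saying which result is meant.
- **Text below Table 4, minimising false positives.** For a positive PCR, "it can be considered a false positive if the IgG result is negative at both baseline and 28 days", with further conditions.
- **Baseline assessments.** For adults, "study visits will follow the same protocol whether current or past COVID-19 is suspected: the analysis will be different".

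Adults are asked for blood at baseline and again at day 28, the second visit being offered where feasible.

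**The concern.** There are two linked problems. The first is internal consistency. Table 3 tells the analyst which results feed which analysis, and for the enhanced active analysis it leaves out the baseline IgG. Without that result nobody can say whether a day-28 positive is new, whether a titre has risen, or whether IgG was negative on both occasions.

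The second remains once the cell is corrected. Past suspects are included in the enhanced active analysis. Someone whose illness was over before baseline can be correctly PCR-negative and correctly POCT-negative, and still develop or increase IgG over the next 28 days. The rule calls that person a missed current infection. The POCT is then charged with a false negative, so its sensitivity against composite standard 1 is biased downward. That standard is meant to correct errors in the PCR reference, so an error of this kind works against its purpose.

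**Working it through.** **1. Can the stated rules be applied with the data Table 3 supplies?**

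| Rule for current infection | IgG results needed | Supplied by Table 3 |
|---|---|---|
| Minimise FN, Table 4 | day 0 negative, day 28 positive | day 28 only |
| Minimise FN, text | day 28 positive, and new or higher than at day 0 | day 28 only |
| Minimise FP, Table 4 and text | negative at day 0 and day 28 | day 28 only |

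None can be applied. Table 3 names both visits for enhanced past infection, so it does distinguish one visit from two. The cell conflicts with the rules and is not shorthand.

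**2. Do Table 4 and the text define the same case?** No. A PCR-negative participant with IgG positive at baseline and a higher titre at day 28 is a case under the text but does not fit the table's pattern. The text also leaves out the word positive for the later PCR in both current-infection rules. The table has it, so this is editorial.

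**3. Who is mislabelled under the stated rule?** Take a recovered, PCR-negative past suspect:

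- IgG positive and stable at both visits: not relabelled.
- IgG negative, then positive: labelled currently infected under both definitions.
- IgG positive, then higher: labelled currently infected under the text only.

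In Table 4 the pattern PCR negative with IgG negative then positive appears both as a missed current and as a missed past infection. That pattern therefore does not separate the two conditions, although the text gives separating them as a purpose of the paired samples.

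**4. Illustration of size.** The document gives no figure to reproduce. Inputs from Stopping criteria: sensitivity Se = 90%, specificity Sp = 99%, prevalence π = 30% or 5%. Assumed: r, the share of participants who are recovered, PCR-negative and IgG-positive at day 28; and s, the share of those with new or rising IgG. It is also assumed that all true active cases are identified and everyone has day-28 serology.

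Apparent sensitivity = [π·Se + r·s·(1 − Sp)] / (π + r·s)

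Example, π = 5%, r = 20%, s = 10%: (0.045 + 0.0002) / (0.05 + 0.02) = 0.0452 / 0.07 = 64.6%.

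| π | r | s = 0 | s = 5% | s = 10% | s = 20% |
|---|---|---|---|---|---|
| 30% | 2% | 90.0% | 89.7% | 89.4% | 88.8% |
| 30% | 20% | 90.0% | 87.1% | 84.4% | 79.5% |
| 5% | 2% | 90.0% | 88.3% | 86.6% | 83.4% |
| 5% | 20% | 90.0% | 75.2% | 64.6% | 50.4% |

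**5. The same in counts.** Both planning scenarios imply 60 active cases (200 × 30%; 1200 × 5%), of whom a 90% sensitive test detects 54. If k recovered people are added as cases and all test negative, sensitivity is 54 / (60 + k): 88.5% for k = 1, 80.6% for k = 7 and 79.4% for k = 8. Eight such people would take the estimate below the 80% minimum used as an example under Number of participants.

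**The case against.** The strongest reply is that Table 3 only indexes data sources, while classification is governed by Table 4 and the text below it. Those require seroconversion or a titre rise, both composites are said to use paired results, and adults are bled at both visits. This stands as far as it goes: the cell is probably a slip, and the stated rule protects recovered people with stable IgG.

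A reader might infer something stronger, namely that everyone recovered and seropositive at day 28 becomes a current case. With 60 true cases, 54 detected, and 100 past suspects of whom 20 to 60% are PCR-negative and IgG-positive, sensitivity would be (54 + 0.2)/80 = 68% down to (54 + 0.6)/120 = 46%. The documents do not support this. It needs day-28 IgG to be used alone, and the numbers of past suspects are assumptions. If 10% of those seropositive people had new or rising IgG, the same sums give 54.02/62 = 87% to 54.06/66 = 82%.

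It is also fair that Table 4 is presented as potential and hypothetical, that detail is left to a SAP that is not shown, and that a second composite guards against the opposite error. These points lower the weight of the concern. They do not remove it, because it rests on statements that conflict, not on missing detail.

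The remark under Baseline assessments that the analysis will differ need not contradict the pooling. Table 3 does assign different tests and references to the active and past questions.

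**Conclusion.** The concern holds in a limited form. Three things are certain from the text: the Table 3 cell is incompatible with the composite rules; Table 4 and the text below it define the serological criterion differently; and pooling exposes recovered past suspects with new or rising IgG to being labelled currently infected under composite standard 1. The direction of the resulting bias is downward for sensitivity.

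Its size cannot be computed from the document, which gives neither the share of past suspects nor how many would have new or rising IgG. The illustration shows it could be negligible, or large when prevalence is low and recovered people are common. It concerns only a secondary analysis, in adults with day-28 serology.

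A reader might extend the point to the primary analysis. That is not supported: the primary analysis compares the POCT with PCR and uses no antibody data, and PCR-negative past suspects do not enter its sensitivity denominator. Removing past suspects there would be a design preference, not a required correction.

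**What to change.** 1. In Table 3, change the antibody entry for enhanced active infection to visits 1 and 2.
2. Choose one serological criterion for a missed current infection, either seroconversion only or seroconversion or titre rise, and state it identically in Table 4 and the text.
3. Insert the word positive before the later RT-PCR result in both current-infection rules in the text, to match Table 4.
4. In the enhanced active analysis, make suspected-current participants the main table and show past suspects as a separate stratum. Alternatively, keep both groups but apply the serology criterion only to suspected-current participants.

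Items 1 to 3 are wording changes and need no new data, since baseline blood is already planned. With the first option, item 4 costs some participants, and so some precision, in the main table of that secondary analysis. The primary analysis need not change.
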